The RM design assesses long-term ED symptoms and autonomy-connectedness characteristics, as well as depressive and anxiety symptoms, self-esteem, and quality of life, every 3 months at the beginning, middle, and end of the intervention, along with a 3-month follow-up (4 measurements). After treatment, participants will also be interviewed about their experiences with autonomy-enhancing therapy. The interviews are intended primarily to provide a richer understanding of participants’ questionnaire scores and changes over time, including participants’ experiences with the intervention, how they perceived changes in autonomy-connectedness, well-being, and ED recovery, and whether these experiences are reflected in quantitative assessments. In addition, the interviews will be used to explore the acceptability and feasibility of the intervention and to identify factors relevant to future implementation. As the qualitative component is exploratory and descriptive in nature, interview data will be reviewed and summarized to identify recurring experiences and implementation considerations rather than subjected to an in-depth qualitative analysis. For a study procedure flowchart, refer to Figure 1. The data will be analyzed using mixed models with an unstructured covariance matrix.

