### Analyses

Sample size and statistical power were approximated using G*Power (version 3.1.9.4). To detect a medium effect size (*f*^2^=0.15) in a regression with 7 predictors, 89 independent observations are needed for a power of 0.95 at α=.05. For the SCED analysis, with an intraclass correlation coefficient of 0.2, each participant’s 20 observations yield 4.17 independent observations [45], necessitating at least 22 participants. To ensure robustness, we aim for 30 participants (125 independent observations), achieving a power of 0.99. Considering a 20% dropout rate, we plan to recruit 36 participants. For the RM analysis, assuming 3 observations per participant, we obtain 30×2.14=64 independent observations, resulting in a power of 0.67 to detect a medium effect size (using α=.01).

Differences between individuals in their SCED data will be examined using visual analyses, presenting separate plots for all participants’ measures [46]. Visual analysis will evaluate changes in level, trend, variability, immediacy of effect, overlap between phases, and consistency across participants. Interview data will be used descriptively to better understand participants’ experiences of the intervention and their interpretation of change. The interview data will be reviewed and summarized to identify recurring experiences, perceived benefits and challenges, and considerations relevant to feasibility and future implementation.

The SCED data will be analyzed using a mixed model with 2 treatment periods, incorporating 2 dummy variables (treatment period 1 and treatment period 2, with baseline as the reference). A linear effect of time, centered within each period, represents the average change across periods. A random intercept and an autoregressive error structure will model the covariance structure. The primary hypothesis of the average decrease in ED symptoms is tested with 1 dummy for treatment period (1=treatment period 1 or 2, 0=baseline). This hypothesis will be tested for autonomy-connectedness.

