The RM data for all outcome variables will be analyzed using mixed models. Measurement will be modeled with 3 dummy variables (after treatment period 1, after treatment period 2, and after 3 months, all with baseline as the reference category), and an unstructured covariance matrix will model the random effects. The analyses will focus on the effect of dummy “post,” testing the hypothesis that scores improve compared with baseline. Mediation by autonomy-connectedness will be tested in two steps: (1) adding autonomy-connectedness to the model and (2) conducting a dependent-samples *t* test (1-tailed) comparing autonomy-connectedness after treatment and at the 3-month follow-up with baseline. Mediation will be concluded if (1) autonomy-connectedness affects the outcome variable in the mixed model analysis and (2) autonomy-connectedness improves over time in the *t* test, indicating a joint-significance test of mediation [47].

All analyses will control for ED diagnosis (dummy AN, with BN as the reference category). We will explore whether the development over time of ED, autonomy-connectedness, and the other outcome variables differ between the two EDs.

Hypotheses on change will be tested 1-tailed, with a significance level of .05 for the multiple baseline data and .01 for the RM data to correct for multiple testing. Missing values on the outcome variable do not affect mixed model analyses [45], whereas participants with missing autonomy-connectedness values will be excluded from the mediation analyses.

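### Mediation link 2 uses a complete-pair t test for a change in 3-monthly autonomy-connectedness that the planned mixed model already tests, so the two results can conflict once posttreatment scores are missing

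*Protocol article*

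**What the plan says.** All of this stands in the protocol article, mainly under Analyses.

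- **First test of the change.** "The RM data for all outcome variables will be analyzed using mixed models". Measurement enters as three dummies against baseline, "an unstructured covariance matrix will model the random effects", and the focus is the post dummy, "testing the hypothesis that scores improve compared with baseline".
- **Autonomy-connectedness is one of these outcomes.** Under Design: "The RM design assesses long-term ED symptoms and autonomy-connectedness characteristics". Secondary Outcome Measures lists the ACS-30 in the 3-monthly set. Analyses counts it among the outcomes when it plans to explore whether the "development over time of ED, autonomy-connectedness, and the other outcome variables differ between the two EDs".
- **Second test of the change.** Mediation is tested in two steps. The second is "conducting a dependent-samples *t* test (1-tailed) comparing autonomy-connectedness after treatment and at the 3-month follow-up with baseline", and mediation is concluded only if that t test shows improvement and autonomy-connectedness also affects the outcome in the mixed model.
- **Covariate.** "All analyses will control for ED diagnosis (dummy AN, with BN as the reference category").
- **Missing data.** Missing outcomes are said not to affect the mixed models, while participants lacking autonomy-connectedness values are left out of the mediation analyses.
- **Expected loss.** "Considering a 20% dropout rate, we plan to recruit 36 participants".
- **Level.** Hypotheses on change are 1-tailed, at .01 for the RM data.

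**The concern.** One quantity, the mean change in ACS-30 from baseline to posttreatment, gets two tests that use different sets of people. The mixed model keeps participants who gave baseline and mid-treatment scores but no posttreatment score. The paired t test drops them. One report could therefore state that RM autonomy-connectedness did not improve and, under mediation, that it did, or the reverse.

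The choice of test also affects validity. If leaving depends on how someone is doing at mid-treatment, the people with both scores are a selected group. Their mean change is then biased, whereas the mixed model uses the mid-treatment score to correct for the selection. The mediation conclusion rests on the test without that protection. The paired t test also has no place for the diagnosis covariate that the plan requires in every analysis.

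**Working it through.** **1. The plan's own RM figure.** The article gives no figure for the t test, only a power for the RM analysis. Effective observations per person are m/(1+(m−1)×ICC) = 3/(1+2×0.2) = 2.14, and 30×2.14 = 64. For one coefficient with f² = 0.15, N = 64 and 7 predictors, the noncentral t has noncentrality √(0.15×64) = 3.10 on 64−7−1 = 56 degrees of freedom. At two-sided .01 this gives 0.667, matching the stated 0.67. The figure does not bear on the choice between the two tests.

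**2. Complete data.** With an unstructured covariance, no missing scores and diagnosis as a main effect, the mixed-model contrast is the mean within-person difference, because diagnosis cancels from it. In a simulation with 30 participants and four visits, estimates and t statistics were identical and the tests never disagreed (reference degrees of freedom n−1). Any conflict about posttreatment versus baseline therefore needs missing scores. The absent covariate is a departure from the plan's own rule more than a source of numerical difference.

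**3. Missing posttreatment scores: set-up.** From the article: 36 recruited, 20% dropout (0.20×36 = 7.2, taken as 7), 1-tailed .01. Assumed: all 7 supply baseline and mid-treatment scores, visit correlations are 0.6-0.7, and leaving is either random or weighted by mid-treatment change.
- Paired t test: mean(D)/(SD(D)/√29), with D the posttreatment minus baseline score in the 36−7 = 29 complete pairs.
- Mixed-model contrast: with this missingness pattern it amounts to regressing D on the baseline and mid-treatment scores in the 29, then evaluating at the means of all 36.

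**4. False positives when there is no true change (nominal 1%).**

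| Who leaves | Paired t test | Mixed model |
|---|---|---|
| Poor mid-treatment responders, mild to strong selection | 2.3% to 8.2% | about 1% |
| Good mid-treatment responders | 0.2% | about 1% |

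Under strong selection of poor responders the t test overstates the change by about 0.14 SD; the mixed-model estimate is off by 0.00 SD.

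**5. Disagreement when there is a true change.**
- Random dropout, 0.4-0.5 SD: the tests disagree in about 8-10% of trials, in both directions. At 0.4 SD one run gave 4.1% with only the t test significant and 4.8% with only the mixed model, 8.9% in all.
- Random dropout, power, with small-sample-corrected variances for the mixed model: 0.485 against 0.478 at 0.4 SD (difference 0.007), and 0.722 against 0.706 at 0.5 SD (difference 0.016). That is at most about 2 points.
- Poor responders leaving: with 30 participants, four visits, correlation 0.5, 20% missing and a change of 0.3-0.5 SD, only the t test was significant in 5-7% of trials, and only the mixed model in at most 1%. With 36 participants and strong selection at 0.4-0.5 SD, only the t test was significant in 26-35%.

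All of these concern posttreatment versus baseline. Every correlation and selection mechanism is an assumption; only the sample size, the dropout rate and the level are the plan's.

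**The case against.** The case for leaving the plan as it is has real force, and most of it stands as a limit on the point.

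- **Each conclusion has a named test.** A reader might infer that the plan leaves open which result decides. It does not: RM change is judged by the post dummy, mediation by the t test. What remains is that the two named tests can give different answers about the same change.
- **Primary hypothesis 2 is elsewhere.** A reader might infer that the primary autonomy-connectedness result is at risk. The primary measure is the weekly ACS-30-ST, tested in the single-case mixed model at .05. The ACS-30 is listed as secondary.
- **The exclusion is declared.** The complete-pair t test follows the plan's stated rule for mediation. The rule is open; the difficulty is its consequence.
- **Power.** A reader might infer that the t test is clearly weaker. A comparison with an uncorrected maximum-likelihood contrast suggests about 5 points (0.527 against 0.478 at 0.4 SD), but most of that comes from uncorrected variances.
- **Direction of bias.** A reader might infer that the t test makes mediation too easy to conclude. That holds only if poor responders leave. The Intervention section says practitioners decide on continuation or discharge at 3 months; it does not say which patients leave. If good responders go, the t test rejects too rarely.

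The objection does not dispose of the complete-pair bias, which the planned mixed model avoids when dropout depends on observed scores, or of the conflict with the rule on controlling for diagnosis.

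**Conclusion.** The point holds for the secondary RM data and for link 2 of the mediation rule. The same baseline-to-posttreatment change is tested twice, and the mediation conclusion rests on the version that is more exposed to the dropout the plan itself expects.

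The size depends on who drops out. It is nil at posttreatment with complete data. With random dropout it is a matter of consistency: no bias, about 2 points of power at most, and 8-10% disagreement at a true change of 0.4-0.5 SD. With dropout tied to mid-treatment course, the t test's false-positive rate runs from about 0.2% to about 8% at nominal 1%, while the mixed model stays at about 1%. These figures rest on 7 of 36 missing at posttreatment, correlations of 0.6-0.7, and dropout that depends only on scores already observed. That the t test uses the RM scores at .01 is inferred from its paragraph and its time points. The change is worth making because it removes a bias risk at almost no cost.

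**What to change.** Delete the dependent-samples t test. Take link 2 from the RM mixed model already planned for autonomy-connectedness, adjusted for diagnosis and 1-tailed at .01: its posttreatment-versus-baseline coefficient and, where the t test now covers the 3-month follow-up, its follow-up-versus-baseline coefficient. Reword the criterion for concluding mediation to match. Limit the sentence that excludes participants with missing autonomy-connectedness to link 1, where autonomy-connectedness is a predictor.

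The cost is a few sentences under Analyses. There is one analysis fewer and no new data, and the article expects collection to run until February 2027. One small downside: the two links will rest on slightly different sets of observations, so the number contributing to each should be reported.

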Several considerations support the potential value of autonomy-connectedness: (1) autonomy-connectedness predicts ED recovery [12]; in a longitudinal study, recovered patients showed decreases in sensitivity to others and increases in the capacity for managing new situations compared with patients who did not recover; (2) autonomy-connectedness is transdiagnostic, which is relevant considering the high comorbidity in ED [18]; (3) autonomy-connectedness partly explains sex differences in ED symptom severity [13] and develops during the same life stages (puberty and young adulthood) in which EDs typically emerge [19], with the shift toward independence and separation contributing to sex-specific prevalence differences in mental health issues; (4) autonomy-connectedness promotes a healthy identity by addressing the ego-syntonic nature of EDs, which can contribute to high relapse rates due to strong identification with the disorder [20]; and (5) a well-founded autonomy-connectedness therapy protocol, autonomy-enhancing therapy, exists [21]. Each of these will be elaborated on in the following sections.

The first reason to include autonomy-connectedness in adult ED treatment is that it has been identified as one of the strongest predictors of recovery from ED after 1 year of treatment [12]. Kuijpers et al [12] found that patients who recovered initially had higher sensitivity to others and showed a significant decrease in sensitivity to others along with an increased capacity for managing new situations after treatment when compared with patients who did not recover. These findings indicate that recovered patients benefited from their ED treatment by gaining autonomy.

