### Hypotheses

Throughout autonomy-enhancing therapy, we expect (1) ED symptoms to decrease, (2) autonomy-connectedness to improve (ie, self-awareness and the capacity for managing new situations to increase, and sensitivity to others to decrease), and (3) autonomy-connectedness to mediate treatment success.

We will explore the differences between ED diagnoses (AN and BN) in relation to hypotheses 1 to 3.

Additionally, with respect to the secondary outcomes, we expect increased self-esteem and quality of life and reduced depression and anxiety at the posttreatment assessment compared with the pretreatment assessment.

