### Design

Two designs are combined: a single-case experimental design (SCED) and a repeated measures (RM) design. Given the vulnerable and highly specific population of patients with severe EDs, a SCED was considered more feasible and ethically appropriate than, for example, a randomized controlled trial, as it reduces the number of participants required and avoids withholding treatment from a control group.

A SCED multiple baseline design differentiates between time and intervention effects, with participants serving as their own controls. Experimental control is demonstrated when changes in outcome variables occur consistently after the introduction of the intervention across staggered baselines. Replication of this pattern across participants strengthens causal inference regarding intervention effects. The number of baseline measurements is randomized (ie, the number of measurements before the start of the intervention), varying from 5 to 8 weeks (ie, 5‐8 measuring points). Weekly measurements are taken for the duration of the assigned baseline plus the length of the intervention. The Eating Disorder Examination Questionnaire–Short (EDE-QS) [36] and the ACS-30-ST measure short-term ED symptoms and autonomy-connectedness characteristics, respectively.

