## Discussion

This study addresses the need for better treatments for ED by testing the effectiveness of autonomy-enhancing therapy, a potentially useful addition to ED treatment. On the basis of previous research on autonomy-connectedness and autonomy-enhancing therapy in other clinical populations [12,23], we hypothesize that autonomy-enhancing therapy will contribute to reductions in ED symptoms and improvements in autonomy-connectedness, self-esteem, quality of life, depression, and anxiety. More specifically, we expect increases in self-awareness and the capacity for managing new situations, alongside decreases in sensitivity to others, to contribute to treatment success. If supported, the findings may provide further evidence for the role of autonomy-connectedness as an underlying vulnerability and maintenance factor in ED. Additionally, this study will provide information regarding the acceptability and feasibility of implementing autonomy-enhancing therapy within routine ED treatment, which will inform future effectiveness research and broader implementation.

This study builds on previous findings suggesting that autonomy-connectedness predicts recovery from ED treatment [12], and that disturbances in self-functioning and interpersonal functioning play an important role in ED psychopathology. Existing ED treatments primarily focus on symptom reduction, while difficulties related to identity, self-definition, autonomy, and interpersonal functioning may remain insufficiently addressed. Autonomy-enhancing therapy may therefore complement existing approaches by targeting these broader underlying processes.

A particular strength of this study is its practice-based design within a specialized ED treatment setting, enhancing ecological validity and clinical applicability. In addition, the SCED multiple baseline design enables insight into the treatment process, as opposed to the “black box” effect of a randomized controlled trial.

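### The mediation rule has no stated time order and no treatment contrast, so symptom change that raises autonomy can be declared autonomy mediating the therapy

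*Protocol article*

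**What the plan says.** All references are to the protocol article.

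- **Hypotheses:** the third hypothesis expects "autonomy-connectedness to mediate treatment success".
- **Analyses, RM paragraph:** it opens with "The RM data for all outcome variables will be analyzed using mixed models" and then gives the mediation procedure. Autonomy-connectedness is added to the model, and a 1-tailed paired t test is done "comparing autonomy-connectedness after treatment and at the 3-month follow-up with baseline". The rule follows: "Mediation will be concluded if (1) autonomy-connectedness affects the outcome variable in the mixed model analysis and (2) autonomy-connectedness improves over time". Hypotheses on change in the RM data are tested 1-tailed at .01.
- **Design:** the RM measures of autonomy and eating disorder (ED) symptoms are taken "every 3 months at the beginning, middle, and end of the intervention, along with a 3-month follow-up (4 measurements". For the weekly EDE-QS and ACS-30-ST, "Weekly measurements are taken for the duration of the assigned baseline plus the length of the intervention".
- **Analyses, single-case (SCED) paragraphs:** weekly autonomy is tested by phase as an outcome in its own right, and each participant's weekly measures are plotted. No mediator or lagged term is described for these data.
- **Discussion:** a named strength is that "the SCED multiple baseline design enables insight into the treatment process".

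**The concern.** A joint-significance test supports mediation of a treatment only if path a is the treatment's effect on the mediator and path b is the mediator's effect on the outcome. The rule secures neither.

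For path b, mediator and outcome are measured at the same visits and no lag is stated. A coefficient from such data looks the same whichever variable moves first. For path a, the t test compares later visits with the start of the intervention. There is no control condition, and TAU continues alongside the therapy (Intervention), so the test measures change over time, whatever its source.

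The rival explanation is plausible on the article's own evidence. On an earlier study of ED treatment, the Background says "These findings indicate that recovered patients benefited from their ED treatment by gaining autonomy", and it does not mention autonomy-enhancing therapy there. At stake is one of three main hypotheses, and the Discussion's hope of further evidence that autonomy-connectedness is a vulnerability and maintenance factor.

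**Working it through.** **1. Which data the rule uses.** The steps stand in the RM paragraph, and the t test needs the 3-month follow-up. Weekly measurement ends with the intervention, so that visit exists only in the RM data. That the mediator enters concurrently is a reading: the text says only that it is added to the model.

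**2. The plan's own figures.** No power or error rate is given for the mediation rule. The nearest figure is RM power. It reproduces: 3/(1 + 2 × 0.2) = 2.14 effective observations per person, 30 × 2.14 = 64, and power 0.667 (two-sided, α = .01, f² = 0.15, 7 predictors) against the stated 0.67. It concerns one regression coefficient, not the joint rule.

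**3. The rule under pure reverse causation (simulation; all effects assumed).** There were 30 participants, 4 visits and 2,000 trials per cell. The model was ED on three visit dummies, diagnosis and concurrent uncentred autonomy, with unstructured covariance. Step 1 and the t test (end of treatment against baseline) were each 1-tailed at .01. ED falls without any therapy effect, autonomy = −b × ED + noise, and autonomy has no effect on ED. Baseline SDs are 1, so the mean autonomy gain is b × ED fall, from 0.3 × 0.5 = 0.15 to 0.7 × 1.0 = 0.70 SD.

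| b | ED fall 0.5 | ED fall 0.8 | ED fall 1.0 |
|---|---|---|---|
| 0.3 | 5% | 12% | 18% |
| 0.5 | 15% | 39% | 59% |
| 0.7 | 33% | 69% | 88% |

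Entries are the share of trials in which mediation is wrongly concluded. Step 1 is met in 84% to 100% of trials, so the t test does most of the limiting.

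**4. Shared trend without a link.** With both measures drifting by 0.8, step 1 is met in 1.4%, step 2 in 97.4% and both in 1.3%. The visit dummies absorb the common trend.

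**5. Other settings.** With 4 visits and the mediator centred within person, three reverse-only settings gave 2.5% to 19%. A weekly process sampled at 3 visits, also centred, gave 27% to 60%, and 6% with a weaker reverse effect. When autonomy truly drove symptoms in that last model, the rule concluded mediation in about 20%.

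**6. What the weekly series could add.** It has 5 + 12 = 17 to 8 + 24 = 32 points per person. In simulated data (30 people, 20 weeks, autoregression 0.4, no measurement error, 1-tailed .05), within-person lagged regressions gave:

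| True process | Autonomy→ED flagged | ED→autonomy flagged |
|---|---|---|
| Reverse 0.1 | 4.5% | 79.8% |
| Reverse 0.2 | 1.9% | 100% |
| Reverse 0.3 | 1.1% | 100% |
| Forward 0.2 | 99.9% | 1.8% |

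This is a best case, because the fitted lag is the generating lag. With measurement error at an assumed reliability of 0.8, the false direction was found in 8% to 11% in one set of runs and 18% to 36% in another. At reliability 0.7 it was 10% to 17%, with the true direction found in 46% to 90%.

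**The case against.** Several points limit the concern.

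- A reader might infer that the weekly data are not used for autonomy at all. The Analyses section does test weekly autonomy by phase against randomized baselines, and plots it. A therapy that never moved autonomy could show up there. What is missing is narrower: that result does not enter the mediation rule.
- A reader might infer that improvement under TAU alone satisfies the rule. It does not, as item 4 shows. What is needed is reverse causation, or stable between-person correlation combined with rising autonomy if the mediator is uncentred.
- A reader might take the Background as evidence that recovery drives autonomy. It also calls autonomy-connectedness one of the strongest predictors of recovery, so it leaves direction open.
- Patients enter in remission at a behavioral level (Participants). The symptom fall, and with it the false rate, may lie toward the low end. Applying 1-tailed .01 to step 1 is also an assumption.
- The RM analysis uses the established ACS-30 and EDE-Q and includes follow-up. The weekly ACS-30-ST is still under psychometric evaluation. It would therefore go too far to conclude that a weekly rule should replace the RM rule.
- The Abstract speaks of exploring the mediating role, and the article discloses the missing control condition and the TAU problem.

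These points narrow the claim and its size. They do not supply a time order or a treatment contrast. The listed limitations do not mention direction, and the Analyses section still states when mediation is to be concluded. That is a fixed rule, not a detail left for an analysis plan.

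**Conclusion.** The point holds in a limited form. The stated rule permits a conclusion of mediation that its two steps cannot carry: direction is not tested, and change in autonomy is not separated from change under TAU. Under reverse causation the simulated false-conclusion rate ran from 2.5% to 88%, according to the assumed link, symptom fall and model form. No single figure can be claimed for this trial. The verdict rests on reading the mediator as concurrent, which the article neither states nor excludes. Lagged weekly data would be informative about order, but measurement error can create false lagged paths, so they would not be sole proof.

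**What to change.** 1. **Reword the rule in Analyses.** Replace the statement that mediation is concluded with wording such as: *If both steps hold, the result will be described as an association consistent with mediation; direction, and attribution to autonomy-enhancing therapy, are not established by this analysis.*
2. **Add a weekly mediation analysis.** Take the phase effect on ACS-30-ST, already planned, as path a. Fit within-person lagged models in both directions (ACS-30-ST at week t−1 to EDE-QS at week t, and the reverse), each adjusted for the prior value of its own outcome and for phase. State that autonomy change precedes symptom change only if path a and the forward lag both hold. Always report the reverse lag.
3. **Add a sensitivity analysis for measurement error** over a stated range of reliabilities. Say that the phase contrast also includes the start of last-phase TAU, because baseline runs during day care.

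The cost is modest extra analysis on data already being collected. Collection is projected to finish in February 2027, so the change can be fixed before the final analysis. The downsides are an assumed one-week lag and reliance on the ACS-30-ST, which is why the weekly result should supplement the RM analysis.

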Thus, improving treatment to aid transdiagnostic recovery, societal rehabilitation, and relapse prevention is crucial. Given the associations between autonomy-connectedness and ED symptoms and comorbidity, autonomy-connectedness could be a useful addition to therapy [12-14]. Autonomy-connectedness refers to the capacity to identify, express, and pursue one’s own needs, wishes, and values while maintaining meaningful and reciprocal relationships with others. It reflects both self-direction and interpersonal connectedness, capturing the degree to which individuals can identify and strive for their own needs, considering those of others. Autonomy-connectedness consists of 3 components: sensitivity to others’ wishes, needs, and opinions; self-awareness, the awareness of one’s own wishes, opinions, and needs and the capacity to express these in social interactions; and the capacity for managing new situations, understood as the inclination to explore, and feeling at ease in new situations [15]. Autonomy-connectedness is informed by attachment theory and neoanalytical object-relation theory on the development of gender identity [16], and it understands that healthy psychological functioning implies a strong self as well as strong connectedness to others [15]. Autonomy-connectedness deficits are an important underlying vulnerability factor for developing mental health problems [17].

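### The mediation rule does not separate within-person from between-person association, so it can be met when no within-person link exists

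*Protocol article*

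**What the plan says.** The Analyses section gives the mediation rule in full, in its paragraph on the repeated-measures (RM) data. The two steps are ("1) adding autonomy-connectedness to the model and (2) conducting a dependent-samples" *t* test, one-tailed). The t test is described as "comparing autonomy-connectedness after treatment and at the 3-month follow-up with baseline". The decision rule is: "Mediation will be concluded if (1) autonomy-connectedness affects the outcome variable in the mixed model analysis", together with the second condition that "autonomy-connectedness improves over time in the" t test. The article calls this a joint-significance test.

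On the model that receives the covariate: "Measurement will be modeled with 3 dummy variables", which makes four occasions, and "an unstructured covariance matrix will model the random effects". The level for RM data is .01, one-tailed for hypotheses on change. The text mentions no person mean, deviation or change score for autonomy-connectedness. The only centring in the section concerns time, in the model for the weekly data.

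**The concern.** The coefficient of an undivided time-varying covariate is a weighted average of two slopes. One is between people: those with lower autonomy-connectedness tend to have more symptoms. The other is within people: when a participant's own autonomy-connectedness rises, that participant's symptoms fall. Only the second bears on mediation of treatment success. The occasion dummies remove the average trend, and the covariance structure changes the weights, but neither sets the between-person weight to zero.

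The second condition does not fill the gap. It asks whether autonomy-connectedness improves on average, not whether those who improved more also lost more symptoms. A sample with a cross-sectional correlation and a mean gain can meet both conditions with no within-person coupling. At stake is hypothesis 3, and with it the statement in the Discussion about autonomy-connectedness as a maintaining factor. The tests of hypotheses 1 and 2 are not affected.

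**Working it through.** **1. The article's own figures.** It states no error rate for the mediation rule. Its sample-size arithmetic reproduces and shows which ICC applies:
- Weekly data: 20/(1 + 19×0.2) = 4.17 effective observations per participant; 89/4.17 = 21.4, hence 22 participants.
- RM data: 3/(1 + 2×0.2) = 2.14; 30×2.14 = 64. So ICC 0.2 is used for the RM data as well.

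**2. Inputs.**
- From the article: n=30, four occasions, occasion dummies, diagnosis dummy, unstructured covariance, one-tailed .01, ICC 0.2.
- Assumed, because the article gives no values: between-person correlation -0.3 to -0.7, gain in autonomy-connectedness 0.5 SD, and ICC 0.5 and 0.7 as alternatives to 0.2.
- The true within-person link is set to zero.

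**3. Why the coefficient is not zero.** This is a large-sample calculation for a random-intercept model with unit variances, T=4 and between-person correlation ρ. The sign is immaterial; ρ=0.6 is used.

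Between-person slope = ρ×ICC / (ICC + (1−ICC)/T). Undivided coefficient = (weight of the between-person slope) × (that slope), since the within-person slope is zero.

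| ICC | Between-person slope | Weight | Undivided coefficient |
|---|---|---|---|
| 0.2 | 0.12/0.40 = 0.300 | 0.259 | 0.078 |
| 0.5 | 0.30/0.625 = 0.480 | 0.276 | 0.132 |
| 0.7 | 0.42/0.775 = 0.542 | 0.285 | 0.154 |

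Across the settings tried, the weight is about 25-35% with 4 occasions. With 20 occasions it is about 5%, so the problem lies mainly in the RM analysis, where the rule is placed.

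**4. How often the second condition is met.** For a 0.5 SD gain the noncentrality of the paired t test is 0.5/√(2(1−ICC)) × √30, that is 2.17, 2.74 and 3.54 for ICC 0.2, 0.5 and 0.7. At one-tailed .01 with 29 df, power is about 0.40, 0.61 and 0.85. At ICC 0.2 this low power, not a sound first criterion, holds the joint rate down.

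**5. Simulated false mediation, rule as written** (one-tailed .01, n=30, unstructured covariance, 0.5 SD gain, post-treatment t test):

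| ICC | Correlation -0.3 | -0.5 | -0.7 |
|---|---|---|---|
| 0.2 | 2% | 3% | 5% |
| 0.5 | 5% | 10% | 22% |
| 0.7 | 10% | 19% | 39% |

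Repeat runs differ by up to about 2 percentage points. With 1000 runs, the simulation error at 22% is √(0.22×0.78/1000) = 1.3 points.

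**6. Sensitivity** (ICC 0.5, correlation 0.6).
- Gains of 0.3, 0.5 and 0.8 SD give 6%, 16% and 23%.
- If the follow-up t test must also succeed, the 0.5 SD figure falls from 16% to 12%.

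**7. Bias or chance.** With correlation 0.6 and a 0.8 SD gain:

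| n | ICC 0.2 | ICC 0.5 |
|---|---|---|
| 30 | about 8-9% | 23% |
| 120 | 28% | 69% |
| 500 | 85% | 99% |

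A valid test would stay at or below its level as n grows.

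**8. Rule based on the deviation coefficient.** False mediation is 0-2% in every setting. With a true within-person correlation of 0.4 (ICC 0.5, 0.8 SD gain, no between-person correlation), the corrected rule concludes mediation in about 89% of runs, against 86% for the rule as written.

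**The case against.** **Size at the article's own ICC.** At ICC 0.2 the false rate is only about 2-5%. Part of that is small-sample error in the standard errors under the unstructured covariance: with zero between-person correlation and a 0.8 SD gain, the rule as written gave 1-3%. At the weak end the excess is therefore hardly visible. This stands, and it is why the range is given and no single figure. ICC 0.7 is plausible for trait-like scales but is not in the article.

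**The undivided covariate is inferred.** The article says only that the variable is added to the model, and a full protocol or SAP may specify centring. That is possible. But the article prints a complete decision rule, and on its plain reading the covariate is undivided.

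**Importance.** The abstract describes the mediation analyses as exploring a role. However, hypothesis 3 is stated alongside hypotheses 1 and 2, and the rule says when mediation will be concluded.

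**Stronger readings that the document does not support:**
- A reader might infer that two variables merely improving together would meet the rule. They would not: the occasion dummies take out the shared mean trend, and symptom improvement is not part of the rule. A between-person correlation is needed.
- A reader might infer from the Background ("Given the associations between autonomy-connectedness and ED symptoms and comorbidity") that the result is known in advance. No correlation is given there, the evidence on sex differences is from a community sample, and these participants are in behavioural remission, which may narrow the range.
- A reader might set the paired t test against "All analyses will control for ED diagnosis (dummy AN, with BN as the reference category". Paired differences already cancel any constant effect of diagnosis on level, so this is not a material defect.

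**Conclusion.** The point holds in a bounded form. As printed, the rule can conclude mediation from a stable between-person association plus a mean gain, and it does so more often than its nominal 1%. The excess is small at ICC 0.2 (about 2-5%), moderate at ICC 0.5 (5-22%) and large at ICC 0.7 (10-39%). These figures rest on the assumed correlations of -0.3 to -0.7, the assumed 0.5 SD gain, n=30, and .01 as the level for the first criterion, which is the plain reading for RM data. The rule does not fail in every case; how often depends on quantities the article does not give. Because the rate rises with sample size, more participants would not cure it.

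**What to change.** In the mediation step, replace the single autonomy-connectedness covariate with two: each participant's mean over their available RM occasions, and the deviation from that mean at each occasion. State that criterion (1) is met only if the deviation (within-person) coefficient is significant at the RM level of .01 in the hypothesised direction. Criterion (2) can stay as it is.

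The cost is one extra covariate and possibly a somewhat larger standard error; no detection was lost in the case tested. No new data are needed, and with collection projected to run to February 2027 the wording can still be fixed prospectively. A lagged analysis of the weekly data could support temporal order but is optional. The change does not supply a concurrent control, so a within-person coefficient would still be an association observed alongside usual care.
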